## Abstract

**Objective**: Functional dyspepsia (FD) is frequently treated in Korean Medicine (KM) clinics in South Korea. With the recent inclusion of herbal decoctions (HDs) for FD in the national pilot program for health insurance coverage, the generation of real-world evidence has become an important policy priority. In this study, we aim to evaluate the real-world clinical outcomes and safety of individualized HD-centered KM care in patients with FD in a primary care setting. **Methods**: This multicenter, prospective, single-arm observational cohort study will enroll 150 participants who meet the Rome IV criteria for FD across 23 KM clinics nationwide. Participants will receive individualized HDs, prescribed at the discretion of the attending physicians, as the primary treatment for 4 weeks. Concomitant KM treatments (e.g., acupuncture, moxibustion, and cupping) are permitted as clinically needed to preserve the pragmatic nature of routine care. The primary outcome is the change in the total symptom score on the Nepean Dyspepsia Index, Korean version (NDI-K), at week 4. Secondary outcomes include the Numeric Rating Scale for overall severity, overall treatment effect, and safety monitoring. Statistical analyses will be performed using mixed models for repeated measures to account for repeated observations and missing data. **Discussion**: This study will evaluate the pragmatic outcomes of individualized HD-centered KM care in routine clinical practice, thereby supporting the external validity of its findings. The findings are expected to provide foundational real-world data for the national HD pilot program, and these data may serve as a reference for healthcare policies and clinical decision-making. Clinical Trial Registration: Clinical Research Information Service (registration number KCT0010254); registered on 11 February 2025.

## 1. Introduction

Functional dyspepsia (FD) is a chronic gastrointestinal disorder characterized by symptoms such as postprandial fullness, early satiation, epigastric pain, or epigastric burning. According to the Rome IV criteria, FD is diagnosed when these symptoms occur in the absence of any identifiable structural or organic disease that could explain them, provided that the symptoms begin at least 6 months prior to diagnosis and have been present during the preceding 3 months [1]. A recent large-scale systematic review and meta-analysis estimated the global prevalence of FD to be approximately 7.2% based on the Rome IV criteria [2]. In South Korea, dyspepsia ranked seventh among outpatient conditions in Korean Medicine (KM) clinics according to the 2024 Health Insurance Statistics Yearbook and has consistently remained within the top 10 over the past decade [3]. This sustained high ranking reflects the substantial and ongoing demand for KM treatment and highlights its contribution to the overall healthcare burden in South Korea.

The underlying mechanisms of FD are complex and heterogeneous. The key physiological drivers include gastric dysmotility (e.g., delayed emptying and compromised fundic accommodation), heightened visceral sensitivity, alterations in duodenal mucosal integrity, disturbances in the gut microbiome, and various psychological factors [4]. Given the multifactorial nature of FD, conventional therapies such as proton pump inhibitors (PPIs) and prokinetics often yield suboptimal outcomes, as they typically target only a single mechanism rather than the full spectrum of the disorder [5]. Moreover, the extended administration of pharmacological agents such as PPIs and prokinetics is frequently restricted by concerns about adverse effects, including cardiovascular and metabolic risks [6,7]. Consequently, many patients seek alternative treatment options, resulting in an increased demand for KM treatment.

In KM, FD is managed through individualized interventions, with herbal decoctions (HDs) serving as the core modality. Although various herbal medicines (HMs) have demonstrated clinical efficacy against FD in randomized controlled trials (RCTs) [8,9], these explanatory studies often have inherent limitations in their clinical applicability. Most existing RCTs have been conducted in highly controlled hospital-based settings with rigid inclusion criteria that do not fully account for the complexity of primary care. Specifically, the standardized protocols of traditional RCTs often overlook the individualized nature of KM, in which treatments are dynamically adjusted based on pattern identification (*Bian-Zheng*) and patient-centered factors [10]. Alternative designs such as pragmatic trials or cluster-randomized trials can provide comparative real-world evidence; however, they may still have limitations in fully reflecting the flexible, individualized nature of primary KM practice.

Recently, the South Korean government launched the second phase of a national pilot program to expand health insurance coverage, with FD newly included as a key target condition [11]. This policy shift underscores the need for high-quality real-world data on the utilization, clinical outcomes, and safety of HDs in routine practice. Given the individualized and multimodal nature of primary KM care, a multicenter prospective observational cohort study is well suited to capturing routine clinical outcomes. Therefore, this study aims to evaluate the real-world clinical outcomes and safety of individualized HD-centered KM care in patients with FD across 23 primary KM clinics. Although uncontrolled observational studies have inherent limitations—such as confounding, selection bias, and expectation bias—this study will generate valuable pragmatic evidence to support the ongoing national HD pilot program and offer practical insights for future health policy and clinical practice.

## 2. Methods

### 2.1. Study Registration

The study is registered with the Clinical Research Information Service under the registration number KCT0010254. URL (accessed on 7 July 2026): https://cris.nih.go.kr/cris/search/detailSearch.do?seq=29160&status=5&seq_group=29160&search_page=M.

### 2.2. Study Design

This is a multicenter, prospective observational cohort study designed to collect real-world data from routine clinical practice without randomization or blinding. To better reflect routine clinical practice, participants will receive assessments and treatments as part of routine clinical care based on the physician’s judgment. The study will be conducted at 23 KM clinics in different regions of South Korea (Table S1), with Kyung Hee University Korean Medicine Hospital serving as the coordinating center. Participants will undergo individualized KM treatments as determined by their physician, followed by clinical assessments and patient-reported outcome surveys at baseline (week 0), visit 2 (week 2), and visit 3 (week 4). This protocol was developed and reported in accordance with the Standard Protocol Items: Recommendations for Interventional Trials (SPIRIT) guidelines (Table S2).

### 2.3. Study Participants

#### 2.3.1. Recruitment

Participants will be recruited voluntarily from 23 KM clinics during routine clinical practice. No predefined recruitment quotas will be assigned to the participating centers. Physicians will provide patients who meet the eligibility criteria (Table 1) with a comprehensive information document detailing the scope of the study. Written informed consent will be obtained before any research-related activities commence.

#### 2.3.2. Withdrawal

Participant participation may be terminated if any one of the following criteria are met:Noncompliance with eligibility criteria discovered after enrollment.Withdrawal of consent by the participant or legal guardian.Investigator’s clinical judgment that continued participation is inappropriate.

### 2.4. Interventions

Because this is an observational study, no experimental intervention is assigned or controlled by the researchers. During the 4-week observation period, participants will receive individualized KM treatments, defined as “HD-centered care,” in which tailored HDs serve as the primary therapeutic modality, supplemented by routine individualized KM care as dictated by the attending physician.

Although HDs are flexibly individualized based on pattern identification, representative formulas frequently prescribed in primary care for FD include Banha-sasim-tang, Yukgunja-tang, and Hyangsa-pyeongwi-san [8,9,12]. These traditional formulas are well documented for improving gastrointestinal motility, modulating visceral hypersensitivity, and protecting the mucosal barrier through key bioactive compounds, and they have a well-established safety profile in clinical practice.

In principle, HDs are prescribed in standard dispensing units (typically comprising 20 therapeutic doses yielding 30 packs, designated for administration three times daily), though these may be adjusted according to individual clinical conditions and practice environments. Detailed prescriptions and dosage information—including repeated prescriptions—will be recorded, and patient adherence to HDs will be monitored based on patient-reported remaining pack counts during follow-up assessments.

Other KM treatments administered as part of routine care, such as herbal extract granules, acupuncture, electroacupuncture, moxibustion, cupping therapy, and pharmacopuncture, may also be provided at the treating physician’s discretion. Detailed information on all KM interventions and concomitant medications, including prescription duration, administration frequency, and concomitant treatments, will be thoroughly documented in the electronic case report form (eCRF) to capture treatment exposure and heterogeneity.

### 2.5. Outcome Measures

Clinical assessments are scheduled at baseline (week 0), week 2, and week 4. For participants who are unable to visit the clinic in person at week 2 or 4, assessments may be conducted via telephone interviews to minimize missing data and ensure continuity. Missing outcome data will not be imputed and will be managed within the mixed models for repeated measures (MMRMs).

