### 2.9. Sample Size

This exploratory multicenter observational cohort study will be conducted under routine clinical conditions. Because of the lack of prior data on NDI-K changes in this specific clinical context, a formal power calculation was not performed. Instead, the target sample size was determined based on the design of previous clinical trials for HMs in FD [16] and recruitment feasibility across 23 participating KM clinics.

The dropout rate was conservatively set at 25%. Although previous multicenter clinical trials on FD in KM typically assumed a 20% attrition rate [17], a higher threshold is adopted to reflect the pragmatic nature of this study. Assuming a 25% dropout rate, recruiting 150 participants will yield approximately 112 evaluable participants, ensuring our goal of securing at least 100 fully evaluable cases for the final analysis. Furthermore, based on prior literature in which the standard deviation (SD) of NDI-K score changes was approximately 10–12 points [16], a sample of 112 evaluable participants provides high statistical precision. The expected margin of error for the mean primary outcome change is approximately 1.85–2.22 points at the 95% confidence level, providing reliable parameter estimates for this exploratory study.

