This study has several inherent methodological limitations. First, because this is an observational study without a randomized controlled group, a causal relationship between HD treatment and clinical outcomes cannot be established. Second, the inherent heterogeneity of individualized prescriptions and concomitant KM interventions may complicate the interpretation of the treatment effects. To address potential confounding and heterogeneity, multivariable regression analyses and exploratory subgroup analyses based on concomitant KM interventions will be performed. Third, the 4-week observation period may be insufficient to evaluate the long-term effectiveness and recurrence patterns of FD. Furthermore, loss to follow-up and missing data may occur due to pragmatic primary care factors, such as early symptom resolution, scheduling conflicts, or noncompliance. Finally, because the study relies primarily on patient-reported outcomes in an open-label setting, reporting and expectation biases cannot be excluded.

Despite these limitations, this study provides a practical, standardized framework for generating pragmatic real-world evidence on HD-based care for FD in primary KM settings. This study will serve as foundational, hypothesis-generating evidence to support future pragmatic clinical research and evidence-based healthcare policies integrating KM into public health systems.

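### Telephone follow-up is optional and worded for those unable to attend, so participants who stop coming because they feel better or do not comply need not be called for the week-4 outcome

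*Protocol article*

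**What the plan says.** Section 2.5 (Outcome Measures) of the Protocol article schedules assessments at weeks 0, 2 and 4 and adds one fallback: "For participants who are unable to visit the clinic in person at week 2 or 4, assessments may be conducted via telephone interviews". Its stated purpose is "to minimize missing data and ensure continuity". Section 2.6.3 says that participants will return at weeks 2 and 4, and Table 2 gives each visit a window of 7 days either side. No section requires contact with a participant who simply does not come.

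The Discussion says that "loss to follow-up and missing data may occur due to pragmatic primary care factors, such as early symptom resolution, scheduling conflicts, or noncompliance".

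Section 2.9 (Sample Size) budgets for this loss: "The dropout rate was conservatively set at 25" per cent, so that "recruiting 150 participants will yield approximately 112 evaluable participants".

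Section 2.10 (Statistical Analysis) fits a mixed model for repeated measures (MMRM) to weeks 2 and 4 with baseline as covariate, under missing at random (MAR) and without imputation. Sensitivity analyses are multiple imputation under MAR, delta-adjusted pattern mixture models and the per-protocol set. Assessment mode is to be examined in secondary models. The full analysis set (FAS) requires at least one post-baseline effectiveness measurement.

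**The concern.** The rule for recovering missed assessments does not match the losses that the plan expects. It is limited twice: by the condition of being *unable* to attend and by the word *may*. Of the three reasons in the Discussion, a scheduling conflict fits the condition. Early symptom resolution and noncompliance describe people who may be able to attend and choose not to, and nothing obliges a site to call them.

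Those two reasons are also the ones most plausibly related to the outcome. If absence depends on how the patient is doing at week 4, beyond what the baseline and week-2 scores show, the MAR-based estimate is biased. Delta-adjusted models show how sensitive the result is to such a departure, but they recover no data. A participant lost before week 2 has no post-baseline score and leaves the FAS altogether. The study has one arm, so no comparator could offset the loss.

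Safety is affected in the same way. Section 2.7 monitors adverse events at visits, with no mandated laboratory tests, so a missed visit without a call is also a gap in adverse event data.

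**Working it through.** **1. Loss reasons set against the telephone rule**

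| Reason in the Discussion | Covered by Section 2.5 as worded? | Plausible link to outcome |
|---|---|---|
| Early symptom resolution | Not clearly: able, but does not come | Yes; losing these understates improvement |
| Scheduling conflicts | Yes | Probably weak |
| Noncompliance | Not clearly: may be able, but does not come | Yes; losing dissatisfied patients may overstate improvement |

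The documents do not split the 25% by reason.

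**2. The plan's own figures**

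Inputs from Section 2.9: 150 enrolled, 25% loss, and "the standard deviation (SD) of NDI-K score changes was approximately 10–12 points".

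- Evaluable: 150 × 0.75 = 112.5, stated as about 112. Lost: 150 × 0.25 = 37.5.
- Margin = 1.96 × SD / √112. SD 10 gives 1.852; SD 12 gives 2.222.

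This reproduces the stated "approximately 1.85–2.22 points at the 95% confidence level". The margin covers random error only.

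**3. Illustrative bias without calls**

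Let d be the average difference in week-4 change between lost and retained participants that the model does not explain. The documents give no value, so d = 2 to 5 points is assumed.

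- Bias = 0.25 × d: 0.25 × 2 = 0.50 and 0.25 × 5 = 1.25 points.
- Coverage of a nominal 95% interval = Φ(1.96 − b/SE) − Φ(−1.96 − b/SE), where b is the bias and SE = SD/√112. For b = 0.50 it is 0.917 (SD 10) and 0.927 (SD 12). For b = 1.25 it is 0.737 and 0.803.
- The bias equals the whole stated margin only when d = 1.852/0.25 = 7.4 points (SD 10) or 2.222/0.25 = 8.9 points (SD 12).

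**4. Illustrative effect of calling every non-attender**

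Assume that calls reach one third or one half of the 37.5, and that those reached are representative of the lost.

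- n = 112.5 + 12.5 = 125, or 112.5 + 18.75 = 131.25.
- Margin, SD 10: 1.75 or 1.71. Margin, SD 12: 2.10 or 2.05. The gain on 1.85 and 2.22 is 0.10 to 0.17 points.
- Residual bias = (0.25 − share of recovered participants in the observed sample) × d. With one third reached: (0.25 − 12.5/125) × d = 0.15d, or 0.30 to 0.75 points. With half reached: (0.25 − 18.75/131.25) × d = 0.107d, or 0.21 to 0.54 points.

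The precision gain is small. Any worthwhile benefit lies in bias and in completeness of adverse event data.

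**The case against.** The strongest case against is that the rule is permissive. It does not forbid calling anyone, its stated aim favours a broad reading of *unable*, and the analysis already expects a mix of telephone and in-person scores. A reader might infer that patients who feel better or stop complying are not called. The text supports only that they need not be. A reader might also infer that most of the expected loss is of this kind. The Discussion names scheduling conflicts as well, which the option covers, and gives no proportions.

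The analysis also handles part of the problem. The MMRM conditions on baseline and on any week-2 score, so improvement or failure already visible at week 2 is taken into account. Missingness related to symptom resolution is therefore not automatically missing not at random; only the residual dependence is. The delta-adjusted models probe that residual, and the Discussion discloses the limitation.

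On size, 25% is a deliberately cautious ceiling, set above the 20% that Section 2.9 cites as typical, in a plan that already includes the telephone option. Not all of the loss can be recovered: Section 2.3.2 ends participation for withdrawn consent or for ineligibility found later, and ineligible participants are outside the FAS anyway. The reasons pull in different directions, so biases may partly cancel. The study is exploratory and described as hypothesis-generating.

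Finally, the number of call attempts and their logging may properly sit in a fuller document or site manual.

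All of this limits the size and certainty of the point. It does not remove it: the article states a rule, and that rule is narrower than its own purpose and the losses it expects. Modelling cannot replace scores that a call could collect.

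**Conclusion.** The point stands as a cheap improvement, not as an error in the calculations or a contradiction. As worded, telephone follow-up is optional and does not clearly reach two of the three groups that the plan expects to lose, and those two are the ones whose absence is most likely to carry information about outcome.

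The direction of any resulting bias is uncertain and its size cannot be derived from the documents. The illustrative 0.5 to 1.25 points, against a stated margin of 1.85 to 2.22, rests on an assumed average residual difference of 2 to 5 points and on the full 25% loss. A reader might be tempted to put the bias near 2 points, as large as the margin. That would need an average unexplained difference of about 8 points (0.25 × 8 = 2.0) across all lost participants, in one direction, and nothing in the documents supports it. The precision gain of about 0.1 to 0.2 points rests on an assumed reach of one third to one half and would not justify the change by itself.

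**What to change.** Reword the telephone provision in Section 2.5 so that week-2 and week-4 assessments *will* be sought by telephone from every participant who does not attend within the visit window, whatever the reason, unless consent to contact has been withdrawn. At minimum this should obtain the week-4 NDI-K total symptom score, together with the NRS, OTE and adverse events. Record the reason for non-attendance and the assessment mode. The recorded reasons would also help to ground the delta values in the pattern mixture models.

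The cost is one sentence of protocol text and a few dozen short calls: 37 or 38 participants at the 25% ceiling, hence at most about 75 calls to complete if every one of them missed both visits (2 × 37.5), plus any repeat attempts. The downside is a somewhat larger share of telephone scores, which Section 2.10 already plans to examine. Section 2.11 expects recruitment to run to 31 December 2028, so the change can still benefit participants yet to be enrolled. The date of the change should be recorded, because follow-up before and after it will differ.

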#### 2.5.1. Primary Outcome Measure

The primary outcome is the change in the total symptom score of the Korean version of the Nepean Dyspepsia Index (NDI-K) from baseline to week 4. The NDI-K is a validated tool for quantifying the severity of dyspeptic symptoms and their impact on patient well-being. This study will use a 15-item symptom subscale that captures the frequency and intensity of discomfort; higher cumulative values represent a greater symptom burden [13]. As the original NDI comprises distinct symptom and quality-of-life subscales, this study specifically uses the 15-item Nepean Dyspepsia Symptom Index (NDSI) as the primary outcome measure to precisely evaluate core physical discomforts associated with FD, independent of general quality-of-life domains. In accordance with established clinical trial standards employing the NDSI [14], therapeutic efficacy will be evaluated primarily through continuous score reductions in this symptom subscale.

#### 2.5.2. Secondary Outcome Measures

Individual NDI-K Scores: Changes in the scores of each of the 15 symptom items.Numeric Rating Scale (NRS): An 11-point scale (0–10) assessing overall dyspepsia severity.Overall Treatment Effect (OTE): A 7-point Likert scale assessing global improvement. Participants classified as “much improved” or “very much improved” on the OTE scale will be defined as treatment responders, and the proportion of responders at week 4 will be analyzed as a secondary outcome [15].

### 2.6. Study Procedure

The study procedure is summarized in Table 2. The total study duration for each participation is 4 weeks.

#### 2.6.1. Screening and Consent

Physicians will explain the research objectives in detail, including the potential risks and therapeutic expectations. Written informed consent will be obtained before collecting any study-specific data. Baseline data encompass comprehensive medical histories, including preexisting conditions and current medication profiles. To satisfy the endoscopy requirement, documentation of an upper gastrointestinal endoscopy performed after symptom onset must be verified. Candidates without a documented post-symptom-onset endoscopy are ineligible for enrollment.

